##### Methods of Delivery

Using the REST mobile app can identify conditions that further lead to pathological conditions from the beginning of pregnancy monitoring. Pathological conditions that are immediately resolved can facilitate a normal delivery.

##### Birth Weight of the Baby

In addition to monitoring the mother’s condition, using the REST mobile app can help monitor the health of the fetus as well. The group that used the app paid more attention to the development of the fetus and could anticipate that the baby’s birth weight can reach a normal value of ≥2500 g.

##### Antenatal Care Visits

The REST mobile app records how many maternal examination visit are made to health facilities. Mothers with the REST mobile app who did not undergo examinations in accordance with the minimum ANC visit standard of ≥6 received a notification from their midwives to immediately carry out the examination.

#### Secondary Outcomes

Monitoring using the REST mobile app makes pregnant women play an active role in their pregnancy conditions, including recording examination results independently, so that their knowledge of examination results increases. The pregnant women’s perception of the current pregnancy by monitoring using the REST mobile app will be better. Because mothers will easily monitor their condition, they will understand every health development experienced. The app used by midwives and pregnant women for pregnancy monitoring was evaluated by assessing satisfaction with all aspects of use.

In addition to maternal and child health indicators, this study assessed secondary outcomes related to the impact of the REST mobile app on health systems. Specifically, we evaluated midwives’ perceived workload, workflow changes, and time efficiency through qualitative methods, such as structured interviews and focus group discussions. These data will provide insights into how the app integrates into routine care, its acceptability among providers, and any unintended consequences on workload. Findings will inform future scale-up strategies and the refinement of app features to ensure that digital tools support rather than burden health care providers.

### Ethical Considerations

This study received ethical approval from the Medical and Health Research Ethics Committee (MHREC), Faculty of Medicine, Public Health and Nursing, Gadjah Mada University – [name] Hospital (approval number KE-FK-0653-EC-2023). ClinicalTrials.gov reviewed this protocol (NCT05741931). Prior to enrollment, all eligible pregnant women were provided with detailed information regarding the study’s objectives, procedures, potential risks, and benefits. The information was delivered in a clear and understandable manner by trained research staff. Written informed consent was obtained from all participants. For those with limited literacy, the information was read aloud, and a witness was present during the consent process to ensure comprehension and voluntary agreement.

To protect the confidentiality and privacy of participants, all data collected from pregnant women and midwives were handled in accordance with established ethical standards and data protection regulations. Personal identifiers were removed and replaced with unique codes to ensure anonymity.

Digital data collected through the REST mobile app were encrypted during both transmission and storage and securely stored on password-protected servers accessible only to authorized members of the research team. Any paper-based data were kept in locked storage within a secure research facility. Participants were informed about these measures during the informed consent process, and all procedures were approved by the Institutional Ethics Review Board.

Participation in this research was voluntary, without any coercion. All participants received comprehensive information about the research, especially about the intervention that would be administered and the possible benefits and risks. Participants were free to withdraw at any time without any impact on their access to health services or a penalty.

### Data Analysis

Descriptive statistics were used to find out the basic characteristics of the entire study group. For bivariable analysis, the independent *t* test or Mann-Whitney U test, and the chi-square test or the Fisher precise test were applied for categorical results, adjusting for group design, if necessary.

Multivariable analysis was performed using mixed effects models to account for clustering at the level of the ANC class cluster. A mixed effects linear regression model was used for sustained outcomes, such as the number of ANC visits and birth weight. Mixed effects logistic regression models were used for binary outcomes, such as pregnancy complications and delivery methods. All models included random interception to account for variations between clusters and fixed effects for interventions, as well as potential confounding variables, including maternal age, education level, socioeconomic status, obstetric history, and nutritional status. Statistical significance was determined using a 2-headed *P* value of <.05.

For each primary and secondary outcome, we used an estimate of the effect size and its precision (95% CIs). Other analyses, including subgroup analysis and customized analysis, of study results were also carried out. Stata 14.0 was used to analyze the data.

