### Sample Size

The sample size for this study was determined based on the following formula of Lemeshow [19]:

where n is the number of samples per group, Z_1–α/2_=1.96 (at the level of 95% trust), Z_1–β_=0.842 (at 80% power), p_1_ is the proportion of outcomes in the intervention group, p_2_ is the proportion of outcomes in the control group, and p_1_ – p_2_ is the difference between the 2 proportions to be compared.

Based on the calculation of the sample size from previous studies [4,20-22], p_1_=0.92 and p_1_=0.72, so the minimum sample size for the intervention and control groups was 54 respondents each. In cluster RCT research, it is necessary to consider the *design effect* (DE) in determining the sample size. The formula used is DE = 1 + (m – 1), where m=10 (the average number of samples per cluster) and is the intraclass correlation coefficient, assumed to be 0.05.

Based on the calculation results, a DE of 1.45 was obtained. Furthermore, the sample size that was obtained was multiplied by the DE, resulting in a sample size of 78.3, which was rounded to 79 respondents per group. Therefore, the total number of participants needed was 158, although considering a loss to follow-up of ~35% (based on a preliminary study of the attendance of ANC classes in 2019 in Purworejo Regency)*.* Therefore, it was necessary to take a total of 214 (107 participants in the intervention and the control group each) at the beginning of the study through cluster sampling. The number of clusters to be used was 22 groups of pregnant women, so each group needed 9.72 samples, rounded 10 pregnant women in each group.

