### Randomization, Allocation, and Blinding

Sample determination was carried out using a cluster sampling approach. The target population was all inpatient health centers spread across 11 subdistricts in Purworejo Regency. Based on data from the Health Office, 14 inpatient health centers met the inclusion criteria. Of these, 11 (78.6%) were randomly selected, each representing 1 subdistrict. These 11 subdistricts consisting of 22 pregnant class clusters (C1-C22) were randomized into an intervention group (n=11, 50%) and a control group (n=11, 50%) using the compute-generated random allocation method. A list of cluster codes was entered, and a random sequence was used to divide the groups in order. The results of randomization determined that the first 11 clusters in the list were allocated to the intervention group (C1-C11), while the remaining 11 clusters were allocated to the control group (C12-C22). Randomization was carried out by independent researchers to ensure unbiased random allocation.

The group allocation was kept secret until the intervention group received treatment. Blinding was not possible both for the treatment provider (researcher) and for the sample because the monitoring intervention allowed for active interaction between treatment provider and sample. To ensure the accuracy and completeness of the report, this study adheres to the standards set out in CONSORT (Consolidated Standards of Reporting Trials) EHEALTH V1.6 checklist (Multimedia Appendix 1), which includes a detailed description of the digital intervention and research methodology [23]. The timeline of participant participation was developed in accordance with the SPIRIT (Standard Protocol Items: Recommendations for Interventional Trials) statement (Table 2 and Multimedia Appendix 2) [24].

**Table 2 table2:** SPIRIT^a^ checklist–recommended schedule for study participation.

Study period and activities		Enrollment time point	Allocation time point	Postallocation time points				Close-out time point
		Week 1	Week 0	Month 1	Month 2	Month 3	After month 3	

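### Cluster adjustment of the between-arm tests is left optional and the mixed models are not named as primary, although the protocol's own design effect is 1.45

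*Protocol article*

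**What the plan says.** In the protocol article, Data Analysis describes two layers of analysis.

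- **Bivariable tests.** The independent t or Mann-Whitney test and the chi-square or Fisher test "were applied for categorical results, adjusting for group design, if necessary". No criterion for necessity is given.
- **Multivariable models.** These are "mixed effects models to account for clustering at the level of the ANC class cluster": linear for the number of visits and birth weight, logistic for complications and delivery method. The random effect is unconditional here: "All models included random interception to account for variations between clusters and fixed effects for interventions", plus covariates.

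The section then sets a two-sided 5% significance level and promises an effect size with a 95% interval for each primary and secondary outcome. It does not say which layer supplies that estimate or the P value that decides an outcome.

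The unit of randomisation is the class: "These 11 subdistricts consisting of 22 pregnant class clusters (C1-C22) were randomized" to 11 intervention and 11 control clusters (Randomization, Allocation, and Blinding). Sample Size treats clustering as something that must be allowed for. It assumes 10 women per cluster and an ICC of 0.05, and obtains a design effect of 1.45.

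**The concern.** The sample size is enlarged for clustering, but the tests may ignore it. Women in one class share a midwife, a venue and a schedule, so a test that counts them as independent understates the variance of the arm difference. In a trial randomised by class, no data pattern makes adjustment unnecessary. A condition without a rule also lets the choice be made after the data are seen.

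Because the models are not given precedence, an unclustered chi-square result for complications or delivery method could be reported as the trial's finding and still comply with the text. The article lists four primary outcomes, and the inflated error would apply to each one tested this way.

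**Working it through.** **Inputs from the document.** Sample Size: proportions 0.92 and 0.72, z values 1.96 and 0.842, m = 10, ICC = 0.05, loss about 35%. Randomization: 22 classes, 11 per arm. Data Analysis: two-sided 5%.

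**Reproducing the plan's figures.**
- Per group, unpooled formula: (1.96 + 0.842)² × (0.92 × 0.08 + 0.72 × 0.28) / 0.20² = 7.851 × 0.2752 / 0.04 ≈ 54.0. The protocol gives 54.
- Design effect: 1 + (10 − 1) × 0.05 = 1.45, as stated.
- 54 × 1.45 = 78.3, rounded up to 79. Then 79 × 1.35 = 106.65, rounded up to 107 per group and 214 in total, as stated.

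**Type I error of an unadjusted test.** If the true variance is DE times the variance the test uses, a nominal two-sided 5% test rejects under the null with probability 2(1 − Φ(1.96/√DE)). The interval has 1/√DE of the correct width.
- 10 per class: √1.45 = 1.204 and 1.96/1.204 = 1.628, so the error is 10.4%. Coverage is 89.6% and the width ratio is 0.83.
- After 35% loss: 10 × 0.65 = 6.5 per class and DE = 1 + 5.5 × 0.05 = 1.275. 1.96/1.129 = 1.736, so the error is 8.3%. Coverage is 91.7% and the width ratio is 0.89.

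Over an assumed ICC range around the protocol's 0.05:

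| ICC | 10 per class | 6.5 per class |
|---|---|---|
| 0.01 | 6.1% | 5.6% |
| 0.05 (protocol) | 10.4% | 8.3% |
| 0.10 | 15.5% | 11.5% |

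Simulated null trials with 22 classes of 10 at ICC 0.05 agree: 10.6% for an unclustered test of a continuous outcome and 10.1% for an unclustered chi-square test.

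**Class-intercept models: does the reference distribution matter?** The article names neither a z reference nor an estimation method, so both are assumptions here. The simulations used 22 equal classes and no covariates, with 40,000 runs per linear setting and 1,500 per logistic setting (Monte Carlo SE about 0.6 points). The logistic rows vary the outcome proportion.

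| Setting | z reference | t on 20 df |
|---|---|---|
| Linear, ICC 0.05, 10 per class | 7.0% (ML), 6.1% (REML) | 5.2% |
| Linear, ICC 0.05, 7 per class | 6.4% (ML), 5.5% (REML) | 4.8% |
| Linear, ICC 0.01, 10 per class | 5.3% (ML), 4.8% (REML) | 5.0% |
| Logistic, ICC 0.05, 10 per class | 5.9% to 6.3% | 4.5% to 4.9% |
| Logistic, ICC 0.05, 7 per class | 4.4% | 2.9% |

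With 22 − 2 = 20 df the critical value is 2.086 rather than 1.960. 2.086/1.960 = 1.064, so intervals widen by about 6%.

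**The case against.** The strongest reply is that the plan does handle clustering. The sentence on the bivariable tests allows adjustment, the tests are labelled bivariable, and the models that follow always carry a random intercept for the class, which is the randomised unit. On that reading the 10.4% arises only if adjustment is skipped and the unadjusted test is then reported as the effect test. This limits the point and is correct as far as it goes. It does not remove the point, because nothing in the section excludes that route or ranks the models above the tests.

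A reader might infer more: that the P values and intervals of the mixed models are themselves wrong, because no small-sample correction is named and there is no term for subdistrict. The documents do not support this.

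- **Small-sample method.** A condensed article commonly leaves this to an analysis plan, which is not shown here. The possible excess is modest and depends on choices the article does not state.
- **Subdistrict level.** The text describes classes randomised from a computer-generated sequence, with no stratification by subdistrict. Under individual randomisation of classes, simulation (assuming two classes per subdistrict) kept the type I error of a class-level analysis at 4.9% to 5.1%, even with half or all of the ICC between subdistricts. A subdistrict term would matter only if allocation in fact followed subdistrict order or was split within subdistricts. The randomisation section leaves this unclear, since codes C1 to C11 form one arm and C12 to C22 the other. That is a question about the allocation, not an established analysis error.

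Replacing the logistic mixed model with a two-stage cluster-level analysis would likewise be a preference, not a correction.

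**Conclusion.** The point holds for the optional adjustment and the missing precedence of the mixed models. At the protocol's own ICC and class size, an unadjusted between-arm test runs at about 10.4% instead of 5%, with intervals about 17% too narrow. At about 6.5 women per class it runs at about 8.3%. These figures assume equal class sizes, the stated ICC, and that the unadjusted test is the one reported.

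The reference distribution is a secondary, conditional matter. If a large-sample z reference would otherwise be used, the excess is about 1 to 2 percentage points at ICC 0.05 with 10 per class. It is smaller or absent with 7 per class and at low ICC. No fault in the models is established for want of a subdistrict level.

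**What to change.** 1. Delete the words *if necessary*, and use no unclustered between-arm test for any outcome.
2. Take unadjusted effects from the same mixed model with intervention as the only fixed effect.
3. State that the mixed model with a class random intercept is the primary analysis for each outcome and supplies its P value and 95% interval.
4. As a cheap improvement with 22 clusters, use REML with Kenward-Roger or Satterthwaite degrees of freedom for linear outcomes. In the logistic models, use a t reference on about 20 df for the intervention effect.

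The cost is a little analysis work. Step 4 makes intervals about 6% wider, and the t reference can be conservative for binary outcomes in small classes (2.9% in the 7-per-class simulation). The abstract reports that data were analysed in April 2025, so any change made after that should be disclosed as a post-analysis change.

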**Results:**

In July 2023, the REST mobile app was prepared and tested in small community groups, including midwives and pregnant women, through simulation, and in September 2023, the app was further refined based on feedback from these groups and introduced to study participants. The majority of participants were aged 20-35 years (n=168, 76.4%), consistent with national demographic trends. Approximately 185 (84.1%) had secondary education (junior and senior high school), and 57 (25.9%) had tertiary education (college graduates). The participants were evenly distributed across economic quintiles, reflecting diverse socioeconomic backgrounds, and most lived approximately 1 km from a health facility. Ethical approval was obtained in April 2024. Staff training was conducted from July to October 2023. Participants were recruited from November 2023 to January 2024, the intervention was implemented from February to July 2024, and data were collected from August 2024 to February 2025. Data were analyzed in April 2025, and dissemination of results is expected by the end of 2025.

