## Methods

### Study Design

This research is an experimental study with a cluster randomized controlled trial (RCT) design. Cluster RCT is a research design that has multilevel characteristics. Generally, cluster RCT research uses 2 levels, the cluster or group level and the individual level. In this study, the class cluster will include pregnant women and participants of the ANC class. To minimize the risk of selection bias, we implemented the following strategies: (1) randomization at the cluster level was performed after cluster enrollment, and baseline characteristics of participants across the intervention and control groups will be carefully assessed and reported. The research design is described in Table 1.

**Table 1 table1:** Research design.

Group	Activity sequence 1			Activity sequence 2			Activity sequence 3			Activity sequence 4
	Observation	Intervention	Observation		Intervention	Observation		Intervention	Observation	
Control	O_0_^a^	X_0_^b^	O_1_^c^		X_0_	O_2_^d^		X_0_	O_3_^e^	
Intervention	O_0_	X_1_^f^	O_1_		X_2_^g^	O_2_		X_3_^h^	O_3_	

^a^O_0_: early identification in pregnant women in the first class of pregnant women.

^b^X_0_: standard intervention for routine antenatal classes without an app.

^c^O_1_: observations in the second class of pregnant women (trimester 2).

^d^O_2_: observations in the third class of pregnant women (trimester 3).

^e^O_3_: observation of childbirth and the newborn.

^f^X_1_: introduction of the REST (Risk Identification, Evaluation Counseling, Systematic Monitoring, Troubleshooting) mobile app for pregnancy monitoring for mothers and midwives using the 10Tpregnancy examination standard.

^g^X_2_: monitoring pregnant women after using the mobile app.

^h^X_3_: monitoring pregnant women using the mobile app and preparing for childbirth during the third trimester.

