### Population

The target population in this study was all pregnant women in Purworejo Regency. The affordable population was all pregnant women in 11 subdistricts. In total, 14 inpatient health centers were included, which included 22 clusters of ANC classes. Each cluster or class group comprised 10 pregnant women who met the inclusion criteria.

The inclusion criteria were as follows: pregnant women with a gestational age of 20-22 weeks (trimester 2), pregnant women who had a pregnancy examination at a health facility, mothers who planned to stay in the research area for at least the next 2 years, and mothers who were willing to participate in the research by signing an informed consent form.

The exclusion criteria were as follows: chronic diseases that require special pregnancy care, inability to give birth normally, and inability to operate an Android cellphone. The applicant was dropped if she moved outside the research area, could not be contacted after agreeing to provide informed consent, or decided to stop participating in the research.

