## Results

In July 2023, the REST mobile app was prepared and tested in small community groups, including midwives and pregnant women, through simulation. In September 2023, the app was further developed and refined based on the feedback from these small group trials and then introduced to study participants. A total of 22 ANC class clusters were involved, comprising 22 midwives and 220 pregnant women in Purworejo Regency. These were divided into 2 groups: 11 (50%) intervention clusters using the REST mobile app and 11 (50%) control clusters. The majority of participating pregnant women were aged 20-35 years (n=168, 76.4%), consistent with national demographic trends. Approximately 185 (84.1%) had secondary education (junior and senior high school), and 57 (25.9%) had tertiary education (college graduates). The participants were evenly distributed across economic quintiles, reflecting diverse socioeconomic backgrounds, and most lived approximately 1 km from a health facility.

To provide a clearer overview of both completed and planned study phases, Table 4 presents the planned timeline for each phase of the RCT.

**Table 4 table4:** Planned timeline^a^ for study phases.

Phase	Start	End
Ethical approval	April 2023	April 2024
Staff training/preparation	July 2023	October 2023
Participant recruitment	November 2023	January 2024
Intervention implementation	February 2024	July 2024
Follow-up/data collection	August 2024	February 2025
Data analysis	March 2025	June 2025
Report writing/publication	July 2025	December 2025

^a^Dates are tentative and may be adjusted based on field conditions and recruitment outcomes.

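### Gestational age at the start is not a named covariate, although the stated dates allow about 20 to 35 weeks; adding it is a cheap safeguard whose gain the documents do not determine (minor)

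*Protocol article*

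**What the plan says.** **Model.** The Data Analysis section plans mixed models, linear or logistic by outcome: "All models included random interception to account for variations between clusters and fixed effects for interventions". The other fixed effects are "potential confounding variables, including maternal age, education level, socioeconomic status, obstetric history, and nutritional status". Gestational age does not appear.

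**Entry.** The Population section admits "pregnant women with a gestational age of 20-22 weeks (trimester 2").

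**Calendar.** The Abstract (Results) states: "Participants were recruited from November 2023 to January 2024, the intervention was implemented from February to July 2024". Table 4 gives the same months, with the footnote "Dates are tentative and may be adjusted based on field conditions and recruitment outcomes".

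**Schedule.** Table 2 places enrolment and allocation about a week apart. It marks the classes, ANC visits and pregnancy complications in Months 1-3. The Table 1 notes describe O1 as "observations in the second class of pregnant women (trimester 2"), and the Abstract (Methods) has app use begin in the second trimester.

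**Outcomes.** The Study Outcomes section says all results were measured after labour. The visit standard is at least 6 over the whole pregnancy.

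**The concern.** The stated months leave a gap between enrolment and intervention of anything from a day to three months. With a common February start, a woman enrolled early at 22 weeks would be near term by her third class, while one enrolled late would have most of the third trimester ahead.

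The Primary Outcomes section gives anemia, hypertension and chronic energy deficiency as examples of complications. The corresponding measurements (hemoglobin, blood pressure, mid-upper arm circumference) are made at each of three class meetings. Fewer meetings before delivery means fewer chances to detect a condition.

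At stake are precision and protection against chance imbalance between two sets of 11 classes. The value needed is already held, because it decides eligibility, and the app cannot change it.

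**Working it through.** **1. Range at the start, by the calendar.** Inputs: 20-22 weeks at entry (Population); recruitment November 2023 to January 2024 and intervention from February 2024 (Abstract, Table 4). The common start date is an assumption.

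- 1 November to 1 February: 92 days / 7 = 13.1 weeks. Latest case: 22 + 13.1 = 35.1 weeks.
- 31 January to 1 February: 1 / 7 = 0.1 week. Earliest case: 20 + 0.1 = 20.1 weeks.
- A start on 29 February instead gives 24.1 to 39.1 weeks.

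With even recruitment (assumed), the mean on 1 February is 21 + 13.14/2 = 27.6 weeks. The SD is sqrt(13.14²/12 + 2²/12) = 3.8 weeks. The share at 28 weeks or more is (13.14 − 7)/13.14 = 47%.

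**2. Range at the start, by the schedule.** Table 2 puts about one week between enrolment and allocation, so women start at about 21-23 weeks, SD 2/sqrt(12) = 0.6. The trimester labels agree with this. If the third trimester begins at 28 weeks and classes are 4.35 weeks apart (both assumed), a second class in trimester 2 needs a start before 28 − 4.35 = 23.65 weeks. On a 1 February start only (23.65 − 21)/13.14 = 20% of women would meet that. The two accounts cannot both hold.

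**3. Consequence for complications if the spread is real.** Assume classes at 0, 4.35 and 8.7 weeks and delivery at 40 weeks.

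- The third class falls after delivery if the start is beyond 40 − 8.7 = 31.3 weeks: (13.14 − 10.3)/13.14 = 22% of women.
- With delivery at 39.5 weeks the share is (13.14 − 9.8)/13.14 = 25%. With classes also two weeks later (the third at 10.7 weeks) it is (13.14 − 7.8)/13.14 = 41%.
- If one class detects a condition with an independent probability of 0.10 (assumed), three classes detect it in 1 − 0.9³ = 27% of women and two in 1 − 0.9² = 19%.

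**4. Consequence for visits.** A 13-week recording window is cut short by delivery at 40 weeks when the start is after week 27: (13.14 − 6)/13.14 = 54% of women. This matters only for visits counted in Months 1-3. The number due over a whole pregnancy does not depend on the start week.

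**5. Chance imbalance between arms.** If each class was filled within one month, the class SD is about 3.55 weeks, and the SD of the arm difference in mean gestational age is 3.55 × sqrt(2/11) = 1.5 weeks. If months were mixed within classes, it is about 3.8 × sqrt(2/110) = 0.5 week. The documents do not say how classes were filled.

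**6. Possible gain in the linear models.** Inputs from Sample Size: ICC 0.05 and m = 10, which reproduce the stated design effect, 1 + 9 × 0.05 = 1.45. Let gestational age explain a share b of between-class variance and w of within-class variance (both assumed). Then

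SE multiplier = sqrt{[0.05(1 − b) + 0.95(1 − w)/10] / [0.05 + 0.95/10]}

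| b | w | Multiplier |
|---|---|---|
| 0 | 0 | 1.000 |
| 0 | 0.10 | 0.967 |
| 0.25 | 0 | 0.956 |
| 0.25 | 0.10 | 0.921 |
| 0.50 | 0.20 | 0.835 |

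The table does not carry over to the logistic model for complications.

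**The case against.** **The covariate list is open.** The word *including* makes it illustrative, and a fuller analysis plan may add gestational age. This is fair, so the point is a suggested improvement and not an error. An open list does, however, leave the choice to be made after results are seen.

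**The 20-35 week range is not established.** A reader might take it as what happened. No passage states a common 1 February start, Table 4 calls its dates tentative, and Tables 1 and 2 and the Abstract (Methods) point to a narrow range. This stands. Against it, the Abstract reports the same recruitment and intervention months in the past tense, so the narrow range is not established either.

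**Class-level error and power.** A reader might infer that the spread inflates class-level variance and lowers power by a stated amount. The documents do not support that. It needs classes filled at different times and a share of variance that is nowhere given. The ICC of 0.05 is a total between-class figure, so adding gestational-age variance on top of it is not justified.

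**Visits.** A reader might infer that the visit outcome depends on the start week. Given the whole-pregnancy standard and measurement after labour, that holds only for counts limited to Months 1-3.

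**No bias is shown.** Allocation was randomised, and the intervals already allow for chance imbalance. This stands: the case is one of precision and of conditional balance.

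**Timing.** The Abstract says data were analysed in April 2025, so a term added now cannot be called prespecified. This also stands and shapes the fix.

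**Conclusion.** The point holds as a minor, low-cost improvement. Gestational age is not named, and the stated dates and entry window allow about 20-35 weeks at the start if classes began in February. The schedule tables imply about 21-23 weeks, and the documents do not settle which is true.

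The argument is strongest for complications, which are looked for at up to three class examinations. It is conditional for visits. The size of the benefit is unknown: a multiplier of 1.00 to 0.835 on the standard error in the linear models, resting wholly on assumed variance shares, and no gain if the spread is narrow. The documents support no claim of bias and no definite loss of power.

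**What to change.** 1. Reconcile the calendar (Abstract, Table 4) with Tables 1 and 2 and the trimester labels, and state when classes actually began relative to enrolment.
2. In Data Analysis, add gestational age on one common fixed date as a single linear fixed effect in the complications and ANC-visit models. With 1 February 2024 as the example date, it is gestational age at enrolment plus the weeks from enrolment to that date. The allocation date is a poor choice: under Table 2 it falls about a week after enrolment and would miss most of the spread.
3. Do not use gestational age at delivery or any other value set after allocation.
4. Report gestational age on the fixed date by arm in the baseline table that Study Design already promises. Together with the actual class start dates, this would show how wide the spread was.
5. If the analysis has already been run, keep the stated model and present the adjusted one beside it as a labelled sensitivity analysis.

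**Cost.** One degree of freedom and no new data. If all women started within about a week of enrolment, expect little or no gain.
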